#### Analyses

The primary analysis will be the mean difference in changes from baseline in all outcome variables between the two groups at three months, using all available results but without imputation of missing data. We will perform an adjusted analysis using regression of outcome on randomised group, adjusted for baseline value of outcome and other variables (e.g gender, education). Secondary analyses will include all randomised individuals (1) by assuming that non-responders have no change in their alcohol consumption, (2) by imputing missing outcomes using other outcomes and website use data, and (3) by considering plausible arm-specific differences between responders and non-responders [38]. Non-response bias will be explored in terms of trend in outcome across number of reminders needed for response [39], and predictors of non-response in terms of baseline characteristics and web usage [40].

Subgroup analyses will be performed by assessing interactions of the primary outcome with a maximum of three pre-determined factors (education, gender, and baseline alcohol consumption). Additional exploratory analyses will be undertaken for the secondary outcomes.

Additional analyses will include descriptive statistics to characterise participants in terms of demographics, alcohol consumption, intention and self-efficacy to change, EQ-5D, and secondary outcome measures; CONSORT diagram [41] of the flow of participants through the trial, and proportion who completed each registration stage to trial entry; and use of intervention and comparator web-sites.

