### Analyses

#### Sample size calculation

The principal end-point is at three months. The primary outcome is the last week's total alcohol consumption in units of alcohol. The observed mean reduction in weekly alcohol consumption in the cohort study was 35% in men (from 39 units in week 1 to 25 units in week 6) and 17% in women (from 24 to 20 units) [26]. A 20% reduction, irrespective of initial level, is typical of non-internet brief interventions [9]. The standard deviation of weekly alcohol consumption in the cohort study was slightly less than the mean, in both men and women, and at both baseline and follow-up. Making a conservative assumption that the standard deviation is equal to the mean, 430 subjects providing follow-up data at three months in each arm would give us 90% power at the 5% significance level to detect a 20% reduction in the past week's alcohol consumption.

Follow-up rates in the cohort study were only 16.5% at 6 weeks [26], but we expect the measures designed to improve retention will achieve follow-up on one-third of participants at 3 months. Hence we need to randomise 2,580 subjects (1290 per group). The duration of the trial recruitment phase will be 12 months.

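### The 90% power figure is for comparing three-month means, but the named primary analysis is an unadjusted change score, for which 90% is not assured

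*Protocol article*

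**What the plan says.** The Sample size calculation section defines the target as a level at one time: "The primary outcome is the last week's total alcohol consumption in units of alcohol", and "The principal end-point is at three months". It takes the SD of weekly consumption as equal to its mean. It calls this conservative, because the cohort SDs were a little below the mean at both baseline and follow-up. For an effect of one-fifth lower weekly drinking, it claims that "430 subjects providing follow-up data at three months in each arm would give us 90% power at the 5% significance level". One-third follow-up turns 430 into 1,290 randomised per group.

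The Analyses section names a different comparison as primary: "The primary analysis will be the mean difference in changes from baseline in all outcome variables between the two groups at three months", on available cases without imputation. The next sentence adds: "We will perform an adjusted analysis using regression of outcome on randomised group, adjusted for baseline value of outcome", with further covariates such as gender and education. Secondary analyses, which deal with non-response, are listed after that. The regression is called neither primary nor secondary.

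**The concern.** A difference between arms in mean change has a variance that includes the whole baseline variance, reduced by the covariance between baseline and follow-up. If that correlation is low, the change score is less precise than ignoring baseline altogether; if it is high, it is more precise. The power statement uses no correlation, so it does not describe the analysis that is to decide the trial. Past-week recall is a single week's snapshot repeated three months later, and its correlation need not be high.

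At stake are the accuracy of the power claim and the efficiency of the deciding analysis. A more efficient analysis of the same data is already planned but is not the one named primary.

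**Working it through.** **Inputs from the Sample size calculation.** 90% power; 5% significance (sidedness not stated); a 20% lower mean; SD equal to the mean; 430 analysed per arm.

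**Assumption.** The baseline-to-follow-up correlation r is not in the document, so 0.3 to 0.8 is tried. All figures are normal approximations, two-sided, scaled so that the baseline mean and SD are 1.

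**1. The plan's own figure.** Compare follow-up means of 1 and 0.8, with SDs 1 and 0.8:

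n = (1.960 + 1.282)² × (1² + 0.8²) / 0.2² = 10.507 × 1.64 / 0.04 = 430.8 per arm.

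Power at 430 is 89.9%, and 430 × 3 = 1,290 per group. A one-sided test with common SD 1 gives 429, so 430 alone does not settle the variant. Both versions compare follow-up means.

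**2. Change score, control mean unchanged.** The two arms' change variances sum to

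2 + 1.64 − 2r(1 + 0.8) = 3.64 − 3.6r.

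This equals 1.64, the value behind 430, when r = 2/3.6 = 0.556. At r = 0.5 the sum is 1.84, so n = 10.507 × 1.84 / 0.04 = 483.3, or 484 per arm.

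**3. Change score, control mean and SD both 20% lower by follow-up.** Follow-up SDs are 0.8 and 0.64, and the difference is 0.16. The variance sum is

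2 + 0.64 + 0.4096 − 2r(1.44) = 3.0496 − 2.88r.

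Break-even is r = 2/2.88 = 0.694. Some fall is conceivable: the cohort fell 35% in men and 17% in women. That cohort was uncontrolled, so it does not predict the control arm.

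**4. Regression on arm and baseline.** The residual variances sum to 1.64 − r²(1.8)²/2 = 1.64 − 1.62r². At r = 0.5 this is 1.235, so n = 10.507 × 1.235 / 0.04 = 324.4, or 325 per arm. In scenario 3 the variance sum and the squared difference both scale by 0.64, so the regression figures do not change.

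Power at 430 per arm (n per arm needed for 90%):

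| r | Change, control unchanged | Change, control falls 20% | Baseline-adjusted regression |
|---|---|---|---|
| 0.3 | 73.6% (673) | 61.2% (898) | 92.4% (393) |
| 0.4 | 79.8% (578) | 67.3% (779) | 94.2% (363) |
| 0.5 | 86.4% (484) | 74.4% (661) | 96.2% (325) |
| 0.6 | 92.6% (389) | 82.3% (543) | 98.1% (278) |
| 0.7 | 97.5% (295) | 90.4% (425) | 99.5% (223) |
| 0.8 | 99.7% (200) | 97.0% (307) | over 99.9% (159) |

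At r = 0 the regression falls back to the comparison of follow-up means, at 89.9%.

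**5. Allowing for an SD below the mean.** The article gives no figure, so 0.95 and 0.90 of the mean are assumed. With control unchanged, break-even solves 3.64 − 3.6r = 1.64/k². This gives r = 0.51 for k = 0.95 and r = 0.45 for k = 0.90. Change-score power at r = 0.5 becomes 89.6% and 92.5%. If control falls 20%, it becomes 79% and 83%.

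**The case against.** The strongest reply is that no loss of power has been shown. A reader might infer from the mismatch that the trial is underpowered; the document does not support that. Everything turns on r, which is not given. Above about 0.56 (control unchanged) or 0.69 (control falling 20%), the change score has more than 90% power, and an SD below the mean lowers both thresholds. This stands: the 90% is unsupported for the named analysis, not refuted.

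Second, the regression is already planned and sits before the list of secondary analyses, so its rank is open to interpretation. That is fair, and the inefficiency does not extend to the whole plan. But the sentence that uses the word primary names the change comparison, and the regression is introduced as something further.

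Third, a change score is a valid estimator in a randomised comparison, and an analysis plan not shown may settle the details. Validity is not disputed. The article itself fixes both the primary analysis and the power claim, and the two do not correspond.

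Two further inferences should be resisted:

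- **Non-response bias.** With two-thirds expected to be lost, a reader might suppose that regression protects against arm differences among responders. It does if response depends on the measured baseline, where the change score over-corrects. If response depends on the stable underlying drinking level, adjusting for one noisy week under-corrects and the change score can be the less biased. The article does not say which mechanism applies.
- **Several primary outcomes.** Applying the primary analysis to every outcome might look like several primaries. One primary outcome and one principal time point are clearly named, so little follows from that phrase.

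**Conclusion.** The concern holds as a mismatch between the power claim and the analysis, and it should be fixed. The 430 per arm and 90% power describe a comparison of three-month means; the named primary analysis is an unadjusted difference in change. Over r from 0.3 to 0.8, change-score power at 430 per arm is 74% to 99.7% with control unchanged and 61% to 97% if control drinking falls 20%. It is somewhat higher in both cases if the SD is below the mean. The planned baseline-adjusted regression gives about 92% or more over that range and about 90% at worst at any correlation.

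These results rest on the assumed range of r, SD equal to the mean except where stated, a two-sided test and a normal approximation; a skewed outcome adds uncertainty. The gain from changing is efficiency and a power claim that fits the analysis, not removal of non-response bias.

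**What to change.** Name the regression of three-month past-week units on randomised arm, adjusted for baseline past-week units, as the single primary analysis of the primary outcome. Keep the unadjusted difference in change as a supporting result. State that 430 per arm was calculated for a comparison of follow-up means, so that 90% is approximately a lower bound for the adjusted analysis under the stated assumptions.

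If the change score is to remain primary, state the assumed correlation or SD of change and restate the power for it.

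The first option changes wording only. Both analyses are already planned, and no extra participants or data are needed.

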### Outcome measures

Baseline data to be collected include:

• basic demographic details (completion of the age and gender fields is mandatory while provision of off-line contact details is encouraged but not mandatory);

• highest level of educational attainment;

• total past week alcohol consumption (using the TOT-AL, a specially designed and validated on-line instrument to determine past week alcohol consumption) [32];

• two single item measures of intention to change drinking and self-efficacy in achieving this change;

• the EQ-5D [33] (a five item health status questionnaire devised for health economic analysis);

• and one of 4 secondary outcome measures, measuring different domains of alcohol-related harm.

One of the many methodological challenges in behavioural intervention research is possible reactivity of assessment – that simply completing assessment measures induces change. This issue is particularly acute in brief alcohol intervention research, given the similarities between research assessment and intervention content. Assessment effects have been studied and effect sizes quantified in this field [34,35]. For this reason, we opted to randomly allocate participants to one of 4 secondary outcome measures to minimise the assessment burden. These measures are:

• Alcohol Use Disorders Identification Test (AUDIT) [21] (measuring hazardous or harmful drinking)

• Leeds Dependence Questionnaire [36] (measuring dependence on alcohol)

• The ten-item Clinical Outcomes in Routine Evaluation (CORE-10) [37] (measuring mental health problems, not specific to alcohol)

• Alcohol Problem Questionnaire [24] (measuring problems related to excess alcohol consumption).

We will also explore possible effects on more specific aspects of alcohol consumption, such as binge drinking, derived from the primary outcome measure.

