### Data collection

Data are collected at baseline (prior to randomisation), three months and 12 months. All data collection is done on-line, through the trial website, accessed via a hot-link in an e-mail. The trial website is separate from the intervention and comparator websites, and has a completely different "feel", engendered by use of different colours, different style of presentation, and different content. The trial website is designed to appeal to user altruism, by emphasising the experimental nature of the two different forms of DYD, our ignorance as to which is better, and the importance of follow-up data from all participants to inform future decisions.

A further methodological challenge is the expected high rate of attrition from follow-up. The original cohort study (section 1.4) had a follow-up rate of 16.5% at 6 weeks. We have incorporated a number of features designed to improve this, including:

• The recruitment and consent procedures emphasise the importance of follow-up;

• The trial website appeals to user altruism, and aims to engender a feeling of being part of an important scientific project;

• Three e-mail reminders at seven day intervals to non-responders;

• The use of an appropriate incentive;

• A final (4^th^) reminder to non-responders with a request to complete a simplified version of the primary outcome measure only.

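### The reminder trend used to explore non-response bias changes instrument at the fourth reminder, so at that level reluctance to respond and version of the measure cannot be separated

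*Protocol article*

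**What the plan says.** Four statements in the protocol article bear on this.

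- *Outcome measures*: baseline past-week consumption is collected with the TOT-AL, described as "a specially designed and validated on-line instrument to determine past week alcohol consumption".
- *Data collection*: follow-up non-responders first receive "Three e-mail reminders at seven day intervals to non-responders". The final, fourth contact is a "reminder to non-responders with a request to complete a simplified version of the primary outcome measure only". No change of instrument is mentioned for the first three reminders, and nothing is said about how the simplified version compares with the full one.
- *Sample size calculation*: "The primary outcome is the last week's total alcohol consumption in units of alcohol". About one third of participants are expected to respond at three months.
- *Analyses*: "Non-response bias will be explored in terms of trend in outcome across number of reminders needed for response". The primary analysis in the same section compares changes from baseline, using every available result without imputation. Neither analysis distinguishes responses by version of the measure.

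**The concern.** A trend across reminders treats people who needed more chasing as stand-ins for people who never answered. On that logic the fourth-reminder responders are the closest available proxy for the two thirds expected to be missing. They are also the group asked for a different form of the measure.

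A difference in their reported drinking could reflect who they are, how they were asked, or both, and the planned data cannot tell these apart. If the simplified version reads lower or higher than the TOT-AL, the check could suggest a trend that is absent or mask one that is present.

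A smaller consequence follows for the primary analysis: these responders contribute change scores with the TOT-AL at baseline and the simplified version at follow-up.

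**Working it through.** **The plan's own figure.** The article gives no number for this check, only the sample size for a 20% effect: "430 subjects providing follow-up data at three months in each arm would give us 90% power at the 5% significance level to detect". With a two-sided test (sidedness is not stated) and each arm's SD equal to its own mean (1 and 0.8), n = (1 + 0.64)(1.960 + 1.282)² / 0.2² = 430.8 per arm, which agrees with 430. Inflation for one-third follow-up gives 430 × 3 = 1290 per arm, 2,580 in total. These figures are not in dispute; they supply the expected 2 × 430 = 860 responders.

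**Assumed inputs.** The article does not give the split of responders by reminder or any difference between versions. Assume shares of 45, 22, 13, 10 and 10% at k = 0 to 4 reminders, SD equal to the mean (the article's assumption), no true trend, and a simplified version reading 10% or 20% lower at k = 4 only.

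**Spread and leverage of the reminder variable.**
- Mean k = 0.22 + 0.26 + 0.30 + 0.40 = 1.18
- Var(k) = (0.22 + 0.52 + 0.90 + 1.60) − 1.18² = 3.24 − 1.3924 = 1.8476
- Share of the sum of squares at k = 4: 0.10 × (4 − 1.18)² / 1.8476 = 43%

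**Spurious slope.** A shift s at k = 4 gives slope s × 0.10 × 2.82 / 1.8476 = 0.1526 s. The standard error is 1/√(860 × 1.8476) = 0.025, or 2.5% of the mean per reminder.

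| Shift at reminder 4 | Slope per reminder | Over four reminders | z | 5% test rejects |
|---|---|---|---|---|
| 10% lower | −1.5% | −6.1% | −0.6 | about 9% |
| 20% lower | −3.1% | −12.2% | −1.2 | about 23% |

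A simplified version that reads higher reverses the signs.

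**Masking.** Suppose outcome truly rises 5% of the mean per reminder, so the true value at k = 4 is 1.20. Read 20% low it becomes 0.96, a shift of −0.24, and the fitted slope is 5% − 0.24 × 15.26% = +1.3%. Read 10% low, it is 5% − 0.12 × 15.26% = +3.2%.

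**Other response patterns.** Taking 50/20/12/8/10, 40/20/15/10/15, 20% at each level, and 30/20/15/10/25, reminder 4 carries 40 to 49% of the sum of squares. A 10% shift gives a spurious change of 6 to 9% over four reminders (rejection 10 to 18%); a 20% shift gives 13 to 18% (rejection 24 to 54%).

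**Restricting to 0 to 3 reminders.** Under the 45/22/13/10/10 split, 774 responders remain, with Var(k) = 1.8222 − 0.8667² = 1.071. The standard error is 1/√(774 × 1.071) = 3.5%, and the instrument shift is gone. Root mean square error with no true trend:
- 10% shift: 2.9% for all responders, √(1.5² + 2.5²), against 3.5% restricted
- 20% shift: 4.0% for all responders, √(3.1² + 2.5²), against 3.5% restricted

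Neither fit is uniformly better.

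**Primary analysis.** If 10% of responders in each arm read 20% low, each arm's mean falls by 0.10 × 0.20 = 2% of itself. A 20% contrast then becomes 0.98 × 20% = 19.6%. An additive shift with equal shares cancels altogether.

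**The case against.** The strongest reply is that this is one exploratory check among several. The Analyses section also plans three missing-data analyses of all randomised participants: no change assumed, imputation, and arm-specific differences between responders and non-responders. It further plans to study baseline and web-use predictors of non-response. No decision and no primary estimate is said to depend on the reminder trend. The shift and the response shares used above are assumptions, and under them the spurious slope would usually not reach significance. All of this stands, and it limits the weight of the point.

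Three stronger readings are not supported:

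- A reader might infer that the trend is in raw outcome level pooled over arms, and so says nothing about the arm contrast. The article does not say this. It leaves open whether the trend is by arm or baseline-adjusted, cites a method for it, and analyses outcomes elsewhere as changes from baseline.
- A reader might infer that the simplified version under-reports. Nothing in the article describes how it reads.
- A reader might infer that fourth-reminder responders should be dropped. That would discard the closest proxy for the non-responders and cost precision.

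The reply that handling of version can be left to a fuller document does not dispose of the point. The article itself fixes both the change of instrument and the variable defining the trend, and they collide at the same level.

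**Conclusion.** The point holds as a minor one. Following the stated text, instrument and reluctance are fully confounded at the fourth reminder, the level with the most leverage on the slope. That much is structural and needs no assumption.

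The size is unknown. It rests on an assumed response split and on an assumed 10 to 20% difference between versions, in a direction chosen for illustration. With 10% of responders at the fourth reminder the distortion is of the order of one standard error; it grows if that group is larger. The standard error uses the article's SD-equal-to-mean assumption without baseline adjustment.

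The trend over 0 to 3 reminders is sound. A reader might infer that the primary comparison is materially biased. The documents do not support that: with similar fourth-reminder shares by arm, the illustrated effect is an attenuation of about 2% of the contrast. The sample size is unaffected.

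**What to change.** 1. Record for each follow-up response which version of the measure was completed, as well as the number of reminders sent.
2. Report the reminder trend twice, side by side: in all responders, and in full-TOT-AL responders only (0 to 3 reminders). Present both by arm and adjusted for baseline consumption.
3. Repeat the primary analysis without simplified-version responders as a sensitivity analysis; the analysis of all available results stays primary.
4. Optionally, add the simplified item to the full three-month form, so that the two versions can be calibrated in people who answer both.

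Items 1 to 3 cost one stored field and a few sentences of analysis text. The restricted trend is less precise (standard error about 3.5% against 2.5% per reminder under the assumed split) and omits the most reluctant responders, so it should supplement the full trend. Item 4 adds a slight response burden in a trial where retention is already a stated challenge. The sample size does not change.

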### Health economic analysis

The primary health economic analysis will assess the incremental cost-effectiveness of the full DYD compared to the provision of flat information only from an NHS perspective. The costs of developing the two websites will be derived from actual cost records from the project. The main outcome for the economic analysis will be Quality Adjusted Life Years. This will be obtained from responses to the EQ-5D [33] questionnaire at baseline, three months and 12 months and population values of health states using the area under the curve method [42]. Sensitivity analysis will be conducted using different methods of imputation of missing data and bootstrapping methods will be used to analyse the uncertainty around the calculated incremental cost-effectiveness ratios and cost-acceptability curves.

A secondary analysis will be performed to model the longer term consequences of changes in alcohol consumption on a range of alcohol related consequences. These analyses will be from a societal perspective. This model will be based on primary data from previous randomised controlled trials and observational data combined with existing systematic reviews. Consequences considered will include future impacts on quantity and quality of life, health and other public service resource use and wider social effects. The costs of interventions will also include an estimate of participants' time engaged in the intervention.

